## **6 Randomization and Masking**

Randomization will be designed to yield expected assignment ratio of 1:1 to the prompt vaccination strategy and the deferred vaccination strategy with the use of simple randomization. Randomization list will have been generated by a Statistician using a computer and will be properly kept by a Designated Study Coordinator. Both this Statistician and the Designated Study Coordinator will have no involvement in other parts of the trial. The Investigator who is designated as the Primary Treating Ophthalmologist and is responsible for the management of the subject in this trial will telephone the Designated Study Coordinator to obtain patient assignment information. Throughout the trial, the randomization assignment will not be masked to the Primary Treating Ophthalmologist, but the Primary Treating Ophthalmologist will not have direct access to the randomization list. The randomization assignment will be masked to an adjudication committee who will independently determine the study endpoint events.

## **7 Analysis Population**

### **7.1 Intention-To-Treat Population**

The Intent-To-Treat (ITT) Population will consist of all patients who have undergone randomization in the study regardless of their compliance with the study assignment. For all ITT analyses, participants will be analyzed as randomized.

## **7.2 Per Protocol Population**

The Per Protocol Population will consist of eligible patients who have adhered to randomly assigned vaccination strategy and where study outcomes have been observed.

## **8 Missing Data**

For baseline characteristics, missing values will be expected to be rare, and will not be imputed. In the primary analysis, the follow-up data will be censored at the follow-up encounter reporting the occurrence of primary endpoint event, withdrawal or loss to follow-up, or the final (month 3) visit (whichever is earlier). There is plan to impute missing data for those who withdraw or are lost to telephone follow up before month 3 with the use of multiple imputation in a sensitivity analysis. Analyses on secondary outcomes will be performed without data imputation.

## **9 Baseline Characteristic Analysis**

A CONSORT flow diagram^1 will be used to summarize the randomization, treatment, adherence and follow-up of participants.

In general, baseline characteristics will be presented descriptively in the intention-to-treat population. According to the numerical characteristics of the variables, if the data follow a normal distribution, the mean with standard deviation will be used for statistical description; if the data are skewed, the median with interquartile range will be used for statistical description. Categorical variables will be summarized as numbers with percentages. Tests of statistical significance will not be taken for baseline characteristics.

Descriptive summaries of clinical variables will include age, gender, ethnic group, uveitis etiological and anatomical classification, severity of uveitis (duration, flares in the past year, and best corrected visual acuity of low vision or blindness) and comorbidities.

## **10 Primary Outcome Comparison**

The primary outcome, time to uveitis symptomatic worsening over the course of 3 months of follow-up, will be compared with the Log-rank test. If a participant does not experience the primary endpoint event, they will have their data censored at the encounter where withdrawal or loss to follow-up occurs, or the final (month 3) follow-up encounter (whichever is earlier). For those with primary endpoint event, the censoring time point will be at the specific telephone call encounter (month 1, month 2, or month 3) where the occurrence of primary endpoint event is reported. Follow-up data after month 3 will no longer be included in the analysis, if any. The multiplicative limit method (Kaplan-Meier) will be used to show the cumulative incidence of primary endpoint event. A proportional hazard model (univariate Cox regression) is used to calculate the hazard ratio as well as 95% CI. The proportional-hazards assumption will be checked by means of inspection of a log-log survival plot.

## **11 Analysis of Secondary Outcomes**

### **11.1 General Principles**

The analysis of secondary outcomes will be performed by using an Intent-To-Treat framework within populations whose secondary outcome measures are available. No formal statistical comparisons for the secondary outcomes are planned, and no adjustment for multiple comparisons will be performed. No inferences can be drawn regarding the secondary outcomes, and these results will be descriptively presented as point estimates with unadjusted 95% confidence intervals only.

## 11.2 Analytical Methods

- a. Time to clinically-confirmed uveitis worsening.

A proportional hazard model (univariate Cox regression) will be used to analyze the time to clinically-confirmed uveitis worsening.

- b. Proportion of each reason for symptomatic uveitis worsening.

Descriptive analysis will be used to report the proportions between groups. Difference between proportions as well as its associated 95% CI will be estimated with the Wilson score method.

- c. Proportion of symptomatic uveitis worsening.

Descriptive analysis will be used to report the proportions between groups. Difference between proportions as well as its associated 95% CI will be estimated with the Wilson score method.

- d. Proportion of each reason for clinically-confirmed uveitis worsening.

Descriptive analysis will be used to report the proportions between groups. Difference between proportions as well as its associated 95% CI will be estimated with the Wilson score method.

- e. Time to initiation of step-up treatment.

A proportional hazard model (univariate Cox regression) will be used to analyze the time to initiation of step-up treatment.

- f. Time to treatment interruptions.

A proportional hazard model (univariate Cox regression) will be used to analyze the time to treatment interruptions.

- g. Time to hospitalization for any reasons.

A proportional hazard model (univariate Cox regression) will be used to analyze

the time to hospitalization for any reasons.

- h. Time to hospitalization for ocular disease.

A proportional hazard model (univariate Cox regression) will be used to analyze the time to hospitalization for ocular disease.

- i. Time to laboratory-confirmed COVID-19.

A proportional hazard model (univariate Cox regression) will be used to analyze the time to laboratory-confirmed COVID-19.

- j. Patient adherence, defined as proportion correctly vaccinated for at least one dose or maintaining not vaccinated per protocol throughout the trial.

Descriptive analysis will be used to report the patient adherence between groups. Difference between proportions as well as its associated 95% CI will be estimated with the Wilson score method.

- k. Proportion of vaccinated type and dose.

Descriptive analysis will be used to report the proportion of vaccinated type and dose administered between groups. Difference between proportions as well as its associated 95% CI will be estimated with the Wilson score method.

- l. Proportion of uveitis remission throughout the trial.

Descriptive analysis will be used to report the proportion of uveitis remission between groups. Difference between proportions as well as its associated 95% CI will be estimated with the Wilson score method.

- m. Vaccine inaccessibility, defined as proportion having gone to the vaccination site but refused due to the lack of vaccines, whereby this situation continues until the end of trial.

Descriptive analysis will be used to report the proportion of vaccine

inaccessibility between groups. Difference between proportions as well as its associated 95% CI will be estimated with the Wilson score method.

- n. Reasons for not yet vaccinated until the end of trial among those who should have been vaccinated per protocol.

Descriptive analysis will be used to report the each reason for not yet vaccinated between groups. Difference between proportions as well as its associated 95% CI will be estimated with the Wilson score method.

- o. Change in anterior chamber cells from the Baseline to the end of three months.

Descriptive analysis will be used to report the proportion of two-grade increase in anterior chamber cells (a clinically meaningful change as described by the SUN working group) from the Baseline to the end of three months between groups. Difference between proportions as well as its associated 95% CI will be estimated with the Wilson score method.

- p. Change in vitreous haze from the Baseline to the end of three months.

Descriptive analysis will be used to report the proportion of two-grade increase in vitreous haze (a clinically meaningful change as described by the SUN working group) from the Baseline to the end of three months between groups. Difference between proportions as well as its associated 95% CI will be estimated with the Wilson score method.

- q. Change in best corrected visual acuity LogMAR score from the Baseline to the end of three months.

A generalized estimating equation (GEE) will be used analyze the least-squares mean changes by treatment group with accounting for the correlation between eyes of the same patient and baseline LogMAR score per eye. For non-numerical visual acuities, the following denotations will be used as previously described: finger count (FC) is assigned as 1.7 LogMAR, hand movement (HM) as 2.0

LogMAR, light perception (LP) as 2.3 LogMAR, and no light perception (NLP) as 3.0 LogMAR. Otherwise, numerical visual acuities will be transformed with the formula:  $\log\text{MAR} = -\log_{10}(\text{visual acuity fraction})$ .

- r. Incidence of any systemic adverse event (apart from uveitis related events).

Descriptive analysis will be used to report the incidence of any systemic adverse event.

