## **5 Sample Size**

A two-sided log-rank test with an overall sample size of 1314 subjects (657 in the deferred vaccination group and 657 in the prompt vaccination group) achieves 80.0% power at a 0.050 significance level to detect a hazard ratio of 1.5 when the proportion surviving (no occurrence of symptomatic uveitis worsening) in the deferred vaccination group is 0.9000. The study lasts for 6 time periods of which subject accrual (entry) occurs in the first 3 time periods. The accrual pattern across time periods is uniform (all periods equal). The proportion dropping out of both groups is 0.1500, respectively.

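### The planned between-arm difference in the 3-month proportion with symptomatic worsening is a crude one, slightly biased under either possible denominator; a Kaplan-Meier difference would avoid this at no cost

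*Supplement*

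**What the plan says.** SAP 11.2 c takes the outcome "Proportion of symptomatic uveitis worsening", reports a proportion in each arm, and estimates the difference and its 95% CI by the Wilson score method. It does not name the denominator.

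Four other parts of the SAP bear on it:

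- SAP 11.1 analyses secondary outcomes in an intention-to-treat framework but "within populations whose secondary outcome measures are available". It also says that they are descriptive and support no inference.
- SAP 8 adds: "Analyses on secondary outcomes will be performed without data imputation".
- SAP 13 treats primary-event status as missing for participants who withdraw or are lost before the month 3 encounter, and assumes that these data are missing completely at random.
- SAP 8 and 10 follow a participant with an event only to the encounter at which it is reported, so loss after that point does not make the status missing.

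For the same event, SAP 10 plans a Kaplan-Meier analysis that "will be used to show the cumulative incidence of primary endpoint event", and protocol 9.2 has survival rates calculated per group. Neither plans a difference between the two curves with a confidence interval. On loss, SAP 5 states: "The proportion dropping out of both groups is 0.1500, respectively".

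**The concern.** If the denominator is those with an available outcome, availability depends on the outcome. A participant with an event who is later lost still counts; a participant lost while event-free does not. Dropping only event-free people raises the proportion, and random loss does not cure this. If everyone randomised is the denominator, the lost are in effect counted as event-free and the proportion falls below the true risk. Under either denominator the distortion grows with the amount of loss, so unequal loss between arms also shifts the difference.

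SAP 11.2 c supplies the only planned absolute between-arm effect on the primary event. A report that follows the plan could show a Kaplan-Meier curve and a crude proportion giving different 3-month risks for the same event in the same participants.

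**Working it through.** **Inputs.** All are from SAP 5 unless noted.

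- Test and size: "A two-sided log-rank test with an overall sample size of 1314 subjects", 657 per arm.
- Target: it "achieves 80.0% power at a 0.050 significance level to detect a hazard ratio of 1.5".
- Control arm: the event-free proportion "in the deferred vaccination group is 0.9000". SAP 5 does not say at what time.
- Accrual over 3 of 6 periods; 15% dropout in each arm.
- Follow-up of 3 months per participant (SAP 1).

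**Reproducing the plan's figure, to place the 0.90 in time.** The documents give no figure for outcome c itself, so the check is on 1314.

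- Freedman events: (1.960 + 0.842)² × [(1 + 1.5)/(1.5 − 1)]² = 196.2, rounded up to 197.
- With exponential survival, 0.90 at 3 periods and uniform accrual over 3 of 6 periods, the mean event probability is (0.1458 + 0.2102)/2 = 0.178.
- N = 197/0.178 = 1107, and 1107/0.85 = 1302, within 1% of 1314.

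Placing the 0.90 at 1 or 6 periods gives 527 or 2473 by the same route. Three months is therefore the working assumption. This step is used only to locate the 0.90 in time.

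**True 3-month risks.** Deferred 1 − 0.90 = 10.0%; prompt 1 − 0.90^1.5 = 14.6%; difference 4.6 points.

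**Model for outcome c.** Constant event hazard L and independent constant loss hazard e, per month:

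- deferred L = −ln(0.90)/3 = 0.0351; prompt L = 1.5 × 0.0351 = 0.0527
- 15% loss: e = −ln(0.85)/3 = 0.0542
- observed events E = L/(L + e) × [1 − exp(−3(L + e))]
- event-free completers C = exp(−3(L + e))
- available-case proportion = E/(E + C); all-randomised proportion = E

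**Equal 15% loss, per 657 participants.**

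| Arm | Events | Event-free completers | Lost | Available cases | All randomised | True |
|---|---|---|---|---|---|---|
| Deferred | 60.7 | 502.6 | 93.7 | 10.8% | 9.2% | 10.0% |
| Prompt | 88.8 | 476.8 | 91.4 | 15.7% | 13.5% | 14.6% |
| Difference (points) | | | | 4.9 | 4.3 | 4.6 |

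**Unequal loss (loss rates assumed; the plan expects equal dropout).** Differences are prompt minus deferred, in points.

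| Loss deferred / prompt | Available cases, HR 1.5 | Available cases, no effect | All randomised, HR 1.5 | All randomised, no effect |
|---|---|---|---|---|
| 10% / 20% | 5.6 | +0.6 | 3.6 | −0.5 |
| 20% / 10% | 4.2 | −0.6 | 4.9 | +0.5 |
| 5% / 25% | 6.4 | +1.2 | 3.0 | −1.0 |

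Under independent loss the Kaplan-Meier risks target a difference of 4.6 in every HR 1.5 row and 0 in every no-effect row.

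**Scale.** At equal 15% loss about 563 and 566 cases are available. The standard error of the difference is √(0.108 × 0.892/563 + 0.157 × 0.843/566) = 0.020, or 2.0 points. The same formula gives about 1.9 points in the no-effect rows.

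**Sensitivity to loss timing.** If loss happens only at the monthly encounters, before that month's event is reported, equal 15% loss gives 10.5% and 15.4%. The no-effect shift at 10% / 20% falls from 0.6 to about 0.4 points.

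**The case against.** There is a strong case for leaving this alone.

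- *Absolute risk is already planned.* SAP 10 and protocol 9.2 give censoring-adjusted risks per arm. This stands, so a reader who inferred that the crude proportion is the plan's only absolute figure for the primary event would be wrong. What the plan lacks is a difference of the two Kaplan-Meier risks with an interval.
- *The denominator is an inference.* SAP 11.2 c does not state it, and SAP 11.1 also invokes intention to treat, which SAP 7.1 defines as all randomised. This stands too. A reader might conclude outright that the plan overstates risk in both arms; the documents support that only on the available-case reading. Under the other reading the bias reverses but does not go away.
- *The size is small.* At the planned equal loss the difference moves by 0.3 points against a standard error of 2.0, and with no true effect it does not move at all. The larger shifts rest on assumed imbalances, and protocol 5.8 requires at least three contact attempts per visit. All of this stands.
- *No direction is built in.* A reader might infer a bias against prompt vaccination. Nothing in the documents says which arm will lose more, and reversing the imbalance reverses the shift.
- *The outcome is descriptive.* SAP 11.1 rules out inference, and the decision rule in SAP 4 uses only the hazard ratio. This limits the consequence. SAP 11.1 still commits to publishing a point estimate and interval, and the label does not make the estimate unbiased.
- *Kaplan-Meier also needs loss independent of outcome.* True. The primary analysis already relies on that assumption, and the crude proportion is biased even when it holds.

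**Conclusion.** The point holds as a minor one. The crude proportion in SAP 11.2 c does not estimate the 3-month risk under either denominator, even on the SAP's own assumption that data are missing completely at random. At the planned 15% loss the error is about 0.8 to 1.1 points per arm and 0.3 points in the difference. Under the assumed imbalances the available-case difference shifts by up to about 1.8 points with HR 1.5 (6.4 against 4.6) and 1.2 points with no effect, in a direction set by which arm loses more. Every shift is below one standard error.

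These sizes assume that the 0.90 applies at 3 months, that event and loss hazards are constant, and that loss is unrelated to outcome. Nothing here touches the log-rank test, the Cox hazard ratio or the trial's conclusion. The case for changing it is that the plan already computes a better estimator of the same quantity.

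**What to change.** In SAP 11.2 c, replace the crude comparison with 1 minus the Kaplan-Meier estimate at the month 3 encounter, per arm, in the full ITT population. Report the difference with a 95% CI from the two Greenwood standard errors: difference ± 1.96 × √(SE₁² + SE₂²). Keep the crude event counts in the table and state their denominator. Note that the estimate assumes loss independent of outcome, as the primary analysis does.

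The cost is one or two sentences. The curves are already planned in SAP 10, so no new data are needed, and the primary test and sample size stay as they are.

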### **9.2 Data Analyses**

Analysis methods of each study outcome will be provided in a detailed statistical analysis plan.

Primary analyses will be on an Intention-to-treat (ITT) basis. According to the intention-to-treat principle (ITT), all patients who have been randomized regardless of their compliance with the study intervention and whose primary outcome is available will be included, which is one of the main data sets for the effectiveness evaluation of this study. Given the pragmatic nature of the trial and the expected gaps in data on patient compliance with randomized intervention, we will not consider the per-protocol (PP) analysis as the primary analysis.

The clinical and demographic characteristics of the participants will be summarized with descriptive statistics. Continuous variables will be described with their distribution range, mean, median, standard deviation, and interquartile range, as appropriate. Categorical variables will be summarized as numbers and the proportions.

The primary outcome will be the time to symptomatic uveitis worsening. For the primary outcome, the multiplicative limit method (Kaplan-Meier) is used for univariate survival analysis, the median time to symptomatic uveitis worsening and survival rate of each group are calculated, and the survival rate curve is compared by the Log-rank test.

For the systemic outcomes, the types, number, and incidence of all systemic adverse events during the follow-up period will be described in a tabular form.

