## **2.3 Safety Objectives**

To evaluate the systemic adverse events of the prompt versus deferred vaccination strategies for patients with uveitis.

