q. Change in best corrected visual acuity LogMAR score from the Baseline to the end of three months.

r. Incidence of any systemic adverse event (apart from uveitis related events).

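### Systemic adverse events, the one outcome serving the stated safety objective, is the only item in SAP 11.2 with no planned between-arm measure; extend the SAP's own Wilson difference to it

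*Supplement*

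**What the plan says.** SAP 2.3 states the safety objective: "To evaluate the systemic adverse events of the prompt versus deferred vaccination strategies for patients with uveitis". Protocol 2.4 carries the same objective.

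SAP 3.2 lists one outcome under that objective, item r: "Incidence of any systemic adverse event (apart from uveitis related events").

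The whole method for item r in SAP 11.2 is: "Descriptive analysis will be used to report the incidence of any systemic adverse event". Protocol 9.2 adds that "the types, number, and incidence of all systemic adverse events during the follow-up period will be described in a tabular form". Neither place names a difference, a ratio or a confidence interval.

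The neighbouring items in SAP 11.2 are treated differently. Items b to d and j to p each carry the sentence "Difference between proportions as well as its associated 95% CI will be estimated with the Wilson score method". Items a and e to i each get a Cox model; for item a the wording is "A proportional hazard model (univariate Cox regression) will be used to analyze the time to clinically-confirmed uveitis worsening". Item q gets a GEE reported by treatment group.

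SAP 11.1 sets the general rule for secondary outcomes. No formal comparisons are planned, the analysis uses participants whose outcome measure is available, and "these results will be descriptively presented as point estimates with unadjusted 95% confidence intervals only".

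**The concern.** The objective is worded as one strategy against the other, but the method stops at an incidence. A reader of the trial report would see two percentages, perhaps each with its own interval, and no planned statement of how far apart the arms are or how precisely that is known.

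Two separate intervals are a poor substitute for an interval on the difference, because they can overlap while the difference interval excludes zero. Protocol 1.2 says the trial is meant to guide vaccination recommendations in uveitis, so the size and precision of any excess in systemic adverse events is something users of the result will want. If the measure is chosen only after the data are seen, it is no longer prespecified.

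**Working it through.** **1. Count of methods in SAP 11.2, items a to r.**

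| Method | Items | Number |
|---|---|---|
| Univariate Cox model | a, e, f, g, h, i | 6 |
| Difference of proportions with 95% CI | b, c, d, j, k, l, m, n, o, p | 10 |
| GEE by treatment group | q | 1 |
| No between-arm measure or model | r | 1 |

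6 + 10 + 1 + 1 = 18. Item q names mean changes by group rather than a difference, but its model has a treatment term from which the difference follows. Item r has no model.

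**2. Does SAP 11.1 fill the gap?** Its text speaks of secondary outcomes, whereas SAP 3.2 is headed as covering secondary and safety outcomes, so its reach to item r is open. Suppose it applies. It asks for the point estimate with a 95% CI, and the estimate named for item r is an incidence. That yields one interval per arm and none for the contrast. The SAP writes out the difference sentence for ten other items, so it does not treat 11.1 as supplying a difference by default.

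**3. What the missing estimate would deliver.** The documents state no figure for this outcome that could be reproduced, and no systemic adverse event rate. The inputs are 657 per arm and 15% dropout (SAP 5), with 657 × 0.85 = 558 per arm after dropout. Incidences are assumed.

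I take the Wilson score method for a difference to mean the usual combination of single-proportion Wilson limits. For arm proportions p1 and p2 with Wilson limits (l1, u1) and (l2, u2), and d = p1 − p2:

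- lower = d − √[(p1 − l1)² + (u2 − p2)²]
- upper = d + √[(u1 − p1)² + (p2 − l2)²]

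Half-width of the 95% CI, in percentage points, with equal incidence in both arms:

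| Assumed incidence | 657 per arm | 558 per arm |
|---|---|---|
| 1% | 1.2 | 1.3 |
| 5% | 2.4 | 2.6 |
| 10% | 3.3 | 3.6 |
| 20% | 4.3 | 4.7 |

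With unequal assumed incidences at 657 per arm:

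- 10% vs 5%: 5.0 points (2.2 to 7.9)
- 15% vs 10%: 5.0 points (1.4 to 8.6)
- 2% vs 1%: 1.0 point (−0.4 to 2.5)

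**4. Illustration of overlapping intervals (assumed counts).** Deferred 79/657 = 12.02% (9.76 to 14.73); prompt 105/657 = 15.98% (13.38 to 18.98). The two intervals overlap. The difference is 3.96 points:

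- lower = 3.96 − √(2.60² + 2.71²) = 3.96 − 3.76 = 0.2
- upper = 3.96 + √(3.00² + 2.26²) = 3.96 + 3.76 = 7.7

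The example is fragile. With 103 vs 79, or with 105 vs 81, the interval is −0.1 to 7.4. The same rates at 558 per arm give −0.1 to 8.0. It shows that two arm-wise intervals and a difference interval can tell different stories. It says nothing about what this trial will find.

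**5. Choice of denominator.** Suppose the true incidences were 12% and 16%, and the 15% who drop out were counted as event-free. The table would show 12 × 0.85 = 10.2% and 16 × 0.85 = 13.6%, so the difference would shrink from 4.0 to 3.4 points.

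**The case against.** The strongest reply is that describing adverse events is a deliberate choice. The primary and secondary objectives are to compare, while the safety objective is to evaluate. Protocol 9.2 plans that these events "will be described in a tabular form", and SAP 11.2 r carries this out. SAP 11.1 allows no inference from these outcomes, and anyone with counts by arm can compute the difference. Part of this stands: the lack of a formal test is no fault. But the objective still sets one strategy against the other. Ten other items show that a difference with its CI is compatible with a purely descriptive analysis. A difference that readers can work out later is not prespecified.

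A reader might also infer that the trial has no comparative safety information at all. The documents do not support that. Protocol 1.2 names uveitis relapse as the main potential risk, and symptomatic uveitis worsening is the primary comparison, with a hazard ratio and 95% CI. Clinically confirmed worsening (item a), treatment interruption due to adverse events (item f) and hospitalization (items g and h) all have Cox models. Non-elective hospitalization is itself a seriousness criterion in protocol 7.2.

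Nor do the documents show that a real difference would be missed. The counts in the illustration are invented, and changing two events moves the interval across zero.

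Finally, using every randomized participant as the denominator may look like the natural intention-to-treat choice. For this item it would conflict with the available-data rule in SAP 11.1 and would count dropouts as event-free.

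**Conclusion.** The point holds in a limited form. Item r is the only outcome serving the designated safety objective, and it is the one item of 18 in SAP 11.2 with no planned between-arm measure or model. On its most generous reading, SAP 11.1 adds an interval to each arm's incidence and nothing for the difference. The gap covers systemic adverse events only and leaves the primary analysis untouched.

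At the planned size, the missing estimate would be known to within about 1 to 5 percentage points. That rests on assumed incidences of 1% to 20%, equal in both arms, and on 558 to 657 participants per arm. It is worth correcting because the SAP already contains the method and applies it to ten other outcomes.

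**What to change.** Add to SAP 11.2 r:

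- The incidence of any systemic adverse event is reported by randomized arm.
- The difference between proportions and its 95% CI are estimated with the Wilson score method, as for items b to d and j to p.
- The result is descriptive, with no test.
- The denominator is participants with adverse event data available, in line with SAP 11.1, and the number lacking follow-up is shown by arm.

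The same difference may be shown for participants with a serious adverse event. It would help to state that SAP 11.1 covers item r.

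The cost is one sentence in the SAP and a few table cells. No new data are needed, and the type I error of the primary analysis is not affected.
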